**Fig. 1 Fig1:**
[figure not shown]
Overview of the two study phases

Phase 1 is a mixed-method longitudinal study intended to characterize the caregiver context of infant feeding in low-income families. We hypothesize that non-responsive feeding styles and non-recommended feeding practices will predict steeper infant growth trajectories and obesity status. To test this hypothesis, we will create a cohort of 300 mother-infant pairs to assess variation in mothers’ feeding styles and practices and model the relation of feeding styles and practices to infant growth from 2 to 24 months and obesity at 24 months. We will also obtain feeding data and in-depth information from a subsample of 36 mothers and their identified other caregivers to provide contextual data on other caregivers’ involvement in infant feeding.

Phase 2 will utilize qualitative methods to develop content to be added to EHS’ existing nutrition program to create the enhanced intervention. Approximately 30 EHS-enrolled families and 30 EHS staff will participate in focus groups. This phase also involves a pilot cluster randomized controlled trial comparing the enhanced program to the existing program. Thirty EHS-enrolled mothers will participate in the trial.

Before we started the research, the University of California Riverside Institutional Review Board (IRB) approved all data collection procedures, study instruments, and informed consent documents. Additionally, the study team and EHS programs completed Memoranda of Understanding outlining roles and responsibilities in the partnership.

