#### Statistical analysis

The study will use feeding styles and practices as two-way treatments, resulting in nested mixed models. In such models the fixed effects will be feeding styles (treated as a categorical variable with 5 levels for 5 feeding styles) and practices (treated as factors of composite scores for each feeding practice, such as exclusive breastfeeding and the introduction of solid food). The random effects will be caused by two types of correlations: those due to the infant characteristics, such as weight, and those due to clustering at multiple time points and within sites (infants’ families educated at the same sites). Accordingly, the R squared of the mixed model is expected to be at least 60%. The overall significance level α for a two-sided test is 0.05, and power 80%. Due to item similarities in a construct, the proposed significance level must be adjusted by the Bonferroni correction for multiple comparisons. In this study, the smallest adjusted significance level will be 0.0008 for each item in the construct of feeding beliefs and behaviors (0.05/63 items used in the construct of feeding practices). In addition, the hazard ratio across time points will be 1 for any reference level or group. Under these predefined conditions, the sample size will be 292, which was calculated in G*power 3.1.9.2.

Multiple imputation will be used if more than 5% of data is missing despite our efforts to prevent missing data. We will consider two types of effects: fixed and random. Thus, generalized linear mixed models will be ideal to analyze the data. Feeding styles and practices will be two categorical variables with fixed effects on the growth z score and obesity. Random effects will result from the nested grouping structure of infant families clustering in the same sites (like children in school classes) and the correlation between the variables, such as infant weight, collected from the same subjects across four time points. We will use generalized linear mixed models to examine if and how feeding styles and practices are associated with infant growth and obesity over time, and we will adjust these models for important covariates (e.g., mother’s pregnancy weight and age). Strongly associated items will be kept; all others will be excluded from further data analysis.

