#### Tracking and retention

At the 2-month visit, researchers will explain to participants the importance of maintaining up-to-date contact information, provide a prepaid mailer with a change of address/phone number form, and ask for names and contact information for three additional adults (e.g., nearby relatives, friends) who may be contacted in the event participants become difficult to reach over the course of the study. Participants will receive the study team’s phone, email, and web contact information to communicate any scheduling changes or changes in contact information. To maximize participant retention, we will use our partnership with EHS to track participants who enroll in the study through EHS records, including home addresses and forwarding addresses if families relocate. To minimize travel or other burden on study participants, we will align in-person data collection procedures with the regular EHS site or home visit for EHS participants. As incentives for participation in the survey, participants will receive $30 for visit 1, $40 for visit 2, $50 for visit 3, and $60 for visit 4, the amount increasing over time to encourage continued participation. Prior obesity trials with children had an average retention rate of 86% [69]. Feeding data participants will receive $50 each provision of feeding data. Each dyadic interview participant will receive $30.

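### A cohort of 300 leaves a 2.7% margin over the required 292, so at the cited 86% retention the 80% power is not delivered for 24-month obesity, and no effect size is stated behind 292

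*Protocol article*

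**What the plan says.** All references are to the protocol article, Phase 1.

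- **Error rates.** Statistical analysis: "The overall significance level α for a two-sided test is 0.05, and power 80" (per cent). After Bonferroni correction, "the smallest adjusted significance level will be 0.0008 for each item in the construct of feeding beliefs and behaviors", obtained as 0.05/63.
- **Other listed conditions.** The same section says that "the R squared of the mixed model is expected to be at least 60" (per cent) and that "the hazard ratio across time points will be 1 for any reference level or group".
- **Result.** "Under these predefined conditions, the sample size will be 292, which was calculated in G*power 3.1.9.2".
- **Enrolment.** Project overview: "we will create a cohort of 300 mother-infant pairs". Eligibility and recruitment repeats the 300.
- **Retention.** Tracking and retention: "Prior obesity trials with children had an average retention rate of 86" (per cent). No other retention figure is given for the Phase 1 cohort.
- **Outcomes.** Survey measures names two dependent variables: growth, modelled as a trajectory over the first 24 months, and obesity at 24 months, the last visit.
- **Missing data.** Statistical analysis plans multiple imputation if more than 5% of data is missing.

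**The concern.** The required number and the enrolled number are almost equal, yet follow-up runs for two years and one of the two outcomes exists only at the final visit. The required number carries no stated allowance for loss, and the retention benchmark quoted a few paragraphs later would take the cohort well below it.

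Separately, the article presents 292 as following from its listed conditions, but none of them is an effect to be detected. A reader cannot tell what size of association the study has 80% power to find.

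This matters beyond reporting. The analysis keeps strongly associated items and excludes the rest, and the results shape the Phase 2 intervention. If power is lower than stated, an item that is dropped looks more reliably unrelated to obesity than the data can show.

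**Working it through.** **1. Can 292 be reproduced from the listed conditions?**

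The inputs are alpha 0.05 or 0.0008 (0.05/63 = 0.00079), power 80%, R squared 60% and a reference hazard ratio of 1.

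- *Hazard ratio of 1.* Its logarithm is 0. As an effect to detect it gives no finite sample size. The article attaches it to the reference level, so it is not offered as an alternative.
- *R squared of 60% as an omnibus effect.* f² = 0.60/(1 − 0.60) = 1.5. The noncentral F test for multiple regression at 80% power needs:

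| Predictors | N at alpha 0.05 | N at alpha 0.0008 |
|---|---|---|
| 1 | 8 | 18 |
| 63 | 79 | 100 |
| 83 | 100 | 122 |
| 91 | 108 | 130 |

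The predictor counts are item counts from the two questionnaires: 63, 63 + 20 and 63 + 28. On this reading the most that is needed is about 130.

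- *R squared of 60% as a covariate term.* The article names Poisson regression for obesity. For a standard normal predictor with log rate ratio β and base rate λ, a standard formula is N = (z₁₋α/₂ + z₀.₈₀ √exp(−β²/2))² / (λ β² (1 − R²)). With λ = 1, R² = 0.6, alpha 0.0008 and an assumed rate ratio of 1.47 (β = 0.385), N = (3.353 + 0.842 × 0.964)² / (0.148 × 0.4) ≈ 292. With λ = 0.4, a rate ratio of 1.5 and alpha 0.05, the result is also 292 after rounding up.

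So 292 can be reached, but only by adding an effect that the article does not state. More than one such effect fits.

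**2. What remains at 24 months?**

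- Margin: 300 − 292 = 8, and 8/300 = 2.7%. Retention must be at least 292/300 = 97.3%.
- At the 86% benchmark: 300 × 0.86 = 258, which is 34 (11.6%) below 292.
- Enrolment that would leave 292 at 86%: 292/0.86 = 339.5, so 340.

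**3. Power at the retained number, taking 292 as correct**

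For a single-parameter test, power(n) = Φ[(z₁₋α/₂ + z₀.₈₀) √(n/292) − z₁₋α/₂], with √(258/292) = 0.940.

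- Alpha 0.0008: (3.353 + 0.842) × 0.940 − 3.353 = 0.590, so power is 72%.
- Alpha 0.05: (1.960 + 0.842) × 0.940 − 1.960 = 0.673, so power is 75%.

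The smallest effect detectable with 80% power grows by √(292/258) = 1.064, about 6%, on the scale of the coefficient.

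As a range, 95% retention leaves 285 infants and about 79% power at either alpha. Full retention of 300 gives 81% to 82%.

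**The case against.** **The 86% is not the plan's assumption.** This is right. It is an average from earlier trials, and the article places it after a list of measures meant to improve retention: tracking through programme records, three further contacts, rising payments and visits aligned with the programme. Retention could be better. It would still have to reach 97.3%, and nothing in the article supports that.

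**Growth curves use partial follow-up, and imputation is planned.** This is also right, and it limits the point. An infant seen at 2, 6 and 12 months informs the trajectory, so the loss there is smaller than 258 against 292 suggests. For obesity at 24 months, imputation uses earlier measurements but does not fully restore a missing final outcome.

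**The inputs to 292 may be sound.** A reader might infer that 292 is wrong, or that R squared of 60% and the ratio of 1 have no place in the calculation. The article does not support that. As shown above, R squared can be a covariate term in a Poisson calculation that gives 292. The inputs are incomplete, not shown to be invalid.

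**A condensed article may leave power details to the full protocol.** Some detail, yes. But this article says that the conditions it lists give 292, and those conditions do not determine it. The figures 292, 300 and 86% all stand in the same text.

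**Conclusion.** The point holds for 24-month obesity. The cohort allows 2.7% loss over two years. At the only retention figure cited, about 258 infants are measured at 24 months, and the implied power is about 72% (alpha 0.0008) or 75% (alpha 0.05) instead of 80%.

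This rests on three assumptions: that 292 is correct for whatever effect was used, that the benchmark of 86% applies at 24 months, and that the test has one parameter. Because the effect behind 292 is unstated, true power is unknown, and the percentages are relative to the article's own requirement.

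A reader might go further and conclude that the power claim fails for the whole study. The article does not support that, since the growth analysis retains information from partly followed infants.

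The second part holds in a limited form: the listed conditions do not determine 292, because no alternative effect is named.

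**What to change.** Keep enrolment at 300 and change the text of Statistical analysis and of Tracking and retention:

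1. Declare a retention assumption for this cohort and the number expected at 24 months (258 if 86% is adopted).
2. Restate power for 24-month obesity at that number: about 72% at alpha 0.0008, or 75% at alpha 0.05. Alternatively, give the larger effect detectable at 80% power, in the metric actually used. Say that the growth analysis loses less.
3. Name the G*Power test and the effect size behind 292, and say what part R squared of 60% and the reference ratio of 1 play in it. Do not delete these inputs, and do not bring in a two-group standardised difference unless that was the calculation used.

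The cost is wording only, and a less favourable stated power for obesity.

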#### Survey measures

Infant weight and length will be measured to produce the two dependent variables: infant growth and obesity. Weight will be measured to the nearest 0.1 kg using calibrated Seca scales. Recumbent length will be measured to the nearest 0.5 cm using standard length rods. We will use the Centers for Disease Control (CDC) and Prevention SAS Macros for the World Health Organization (WHO) growth charts to convert weight and length measures into z-scores. WHO reference standards of gender-specific weight-for-length z-scores at ages 2, 6, 12, and 24 months will be used to evaluate infant growth and obesity.

Infant growth will be calculated as the growth trajectory over the first 24 months of life, using growth curve models of weight-for-length z-scores. We will explore the trajectory with different starting points, using the infant’s birth weight-for-length (reported by mother and converted to z-score) as baseline z-scores.

Obesity at 24 months will be calculated by the child’s body mass index (BMI), the standard clinical measure of obesity in children 2 years and older. We will assess this measure as kilograms of weight per square meter of length, and derive age- and gender-specific BMI percentiles, weight-for-age and BMI-for-age z-scores according to US national standards.

Feeding styles will be measured by the Infant Feeding Style Questionnaire (IFSQ), [56] which has 63 items on infant feeding beliefs and behaviors and 20 additional behavioral items related to solid feeding for children over 6 months of age. The questionnaire captures five feeding styles (i.e., laissez-faire, pressuring, restrictive, responsive, and indulgent) previously validated in a low-income sample of parents of infants and toddlers. Feeding practices will be measured by the 28 items (33 at 12 months) from the Baby Basic Needs Questionnaire (BBNQ) [57] pertaining to feeding, such as whether the child is breastfed exclusively or in combination with formula, when breastfeeding ended (if applicable), whether the child is exclusively formula fed, whether the child is fed solid foods, when solid foods were introduced, and what solid foods and other beverages are fed.

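### Questionnaire items are kept or dropped by their association with growth and obesity and then modelled against the same outcomes in the same cohort, with no threshold or validation step; the item-level Bonferroni statement is also mislabelled and is not the smallest level

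*Protocol article*

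**What the plan says.** All of this is in the protocol article, under Phase 1.

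- **Instruments (Survey measures).** Feeding styles come from the Infant Feeding Style Questionnaire (IFSQ), "which has 63 items on infant feeding beliefs and behaviors and 20 additional behavioral items related to solid feeding" for children past 6 months. On its structure: "The questionnaire captures five feeding styles (i.e., laissez-faire, pressuring, restrictive, responsive, and indulgent) previously validated". Practices come from another instrument: "Feeding practices will be measured by the 28 items (33 at 12 months) from the Baby Basic Needs Questionnaire" (BBNQ).
- **Error rate (Statistical analysis).** "The overall significance level α for a two-sided test is 0.05, and power 80" per cent. After a Bonferroni adjustment, "the smallest adjusted significance level will be 0.0008 for each item in the construct of feeding beliefs and behaviors", with the derivation in parentheses: "0.05/63 items used in the construct of feeding practices".
- **Model (same section).** Style enters as a fixed effect with five levels and practices as composite scores. Mixed models are to "examine if and how feeding styles and practices are associated with infant growth and obesity over time", with covariate adjustment.
- **Retention rule (the next sentence).** "Strongly associated items will be kept; all others will be excluded from further data analysis".
- **What follows (last paragraph of the section).** Further mixed models relate constructs and subgroups of styles and practices to growth and obesity. They report effect sizes that compare the constructs' contributions, and the results feed the design of the enhanced intervention.

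**The concern.** The retention rule follows directly on the models of growth and obesity, so the natural reading is that an item survives because it is associated with one of those outcomes. The survivors are then used, in the same infants, to estimate how strongly the constructs relate to the same outcomes. An item whose estimate happens to be high is more likely to be kept, so the kept estimates are on average too large. The section describes no split sample, cross-validation or shrinkage to correct this, and 'strongly' has no cut-off, so the analyst could choose it after seeing the data.

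Two further things are at stake. The IFSQ was chosen for its five validated styles, and a style scored from an outcome-selected subset of items is no longer that scale. The estimates also help decide what goes into the Phase 2 intervention, so overstated items may be given too much weight.

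The Bonferroni statement is a separate and smaller matter: do its item count and label agree with the instruments described under Survey measures?

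**Working it through.** **1. The plan's own level.** 0.05/63 = 0.00079, which rounds to the stated 0.0008. The divisor equals the core IFSQ count in Survey measures, so the figure reproduces.

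**2. Label and 'smallest'.** One sentence assigns the 63 items both to beliefs and behaviors and, in the parenthesis, to feeding practices. Practices are the BBNQ, with 28 items (33 at 12 months). As its own family the BBNQ would give 0.05/28 = 0.0018 or 0.05/33 = 0.0015. Past 6 months the IFSQ has 63 + 20 = 83 items, and 0.05/83 = 0.0006, which is below 0.0008. Using 0.0008 for all 83 gives a familywise bound of 83 × 0.0008 = 0.066, against the declared 0.05.

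**3. Overstatement from selection.** The plan gives no cut-off and no item effect, so both are assumed here. Let an item's test statistic be Z ~ N(m, 1), kept if it exceeds c. For two-sided 0.0008, c = 3.353; the opposite tail is negligible. Then

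power = Φ(m − c), and mean of Z when kept = m + φ(c − m)/Φ(m − c).

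| m | Power | Mean of Z when kept | Ratio to m |
|---|---|---|---|
| 4.194 | 0.80 | 4.194 + 0.280/0.800 = 4.544 | 1.08 |
| 3 | 0.36 | 3 + 0.3749/0.3621 = 4.035 | 1.345 |
| 2 | 0.09 | 2 + 0.1598/0.0881 = 3.814 | 1.91 |

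A simulation on the correlation scale gives the same pattern. It takes n = 292, assumes the item–outcome correlation r, and ignores clustering, repeated measures and attrition. An item must reach |r| of about 0.195 to be kept at 0.0008. Kept items are overstated 2.2-fold at true r = 0.10, 1.5-fold at 0.15, 1.2-fold at 0.20 and 1.06-fold at 0.25.

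**4. False positives depend on the missing cut-off.** Suppose no item is related to the outcome.

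- At p < 0.05 with 63 independent items, the chance that at least one is kept is 1 − 0.95^63 = 0.96. Simulation with inter-item correlation of 0 to 0.3 (assumed) gave 87% to 96%, and in those runs a composite of the kept items was also significant at 0.05 in the same data.
- At 0.0008 the bound is 63 × 0.0008 = 0.050, and simulation gave about 5%.

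So a strict cut-off keeps the false-positive rate near nominal but still overstates kept effects; a loose one loses both.

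**5. Direction of the divisor error.** Moving from 63 to 83 makes the test stricter. At n = 292 and an assumed r of 0.20, power per item falls from 54% at 0.0008 to 51% at 0.0006. Correcting the count therefore costs a little power.

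**The case against.** The best case for the plan has four parts.

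- **The retention sentence is ambiguous.** It names no outcome and no cut-off, and does not say that items are tested one at a time. The last paragraph of the section lists clustering of items into subconstructs as a result, so 'associated' could mean associated with a construct. This has some force, but the preceding sentence is about association with growth and obesity, and the rule excludes items from all further analysis. If another meaning was intended, the text has to say so.
- **The threshold may be in an analysis plan not shown.** That is fair for the numerical cut-off alone. The decision to exclude on association and continue in the same data is a stated rule, and a cut-off would not remove the overstatement.
- **The main model is at construct level.** Style is a five-level factor and the overall level is 0.05. A reader might infer that the styles hypothesis is tested at 0.0008. The text does not say so: 0.0008 is given for items.
- **Phase 2 has other inputs.** Literature, focus groups, advisory-board review and cognitive interviews also shape the intervention, with a fallback to existing literature. This stands, and limits the harm from any one overstated item.

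Three other inferences should be resisted. The miscount does not explain a loss of power, since the corrected divisor lowers power slightly. Pooling both instruments into one divisor is not required, because the plan treats styles and practices as separate constructs. Nor is Bonferroni invalid for similar items: correlation makes it conservative, not wrong.

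**Conclusion.** The concern holds for the retention rule. Followed as written, on its natural reading, it selects items on the outcome, re-estimates in the same cohort and changes the validated scales. The size depends on a cut-off and item effects that the plan does not give. Assuming selection at 0.0008, overstatement is about 8% at 80% power, 34.5% at 36% and 91% at 9%. The larger figures belong to weak items; a well-powered item is little affected. Loss of false-positive control follows only if the cut-off is loose, such as p < 0.05, and the document does not settle which applies.

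The Bonferroni point is a correction of label and scope. The arithmetic is right for 63 core IFSQ items, the feeding-practices label is wrong, and 0.0008 is not the smallest level when all 83 IFSQ items are used (0.0006; familywise bound 0.066 if 0.0008 is kept).

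A reader might also infer a definite power gain from testing five scores instead of items. The documents state no detectable effect, so any such gain rests on assumed effect sizes, including how a score's effect compares with a single item's.

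**What to change.** 1. Delete the keep/exclude sentence.
2. Name the five full IFSQ style scores, scored as validated, as the confirmatory exposures, each at 0.05/5 = 0.01 or by Holm. The sentence that enters style as a single five-level factor needs matching wording.
3. Name the practice composites in advance and treat them as a separate family with its own adjustment.
4. Keep all of these in the model whatever their p-values.
5. Report item-level results as exploratory, including when they are passed to the Phase 2 working group.
6. If an item threshold is retained, use 83 as the IFSQ divisor after 6 months, correct the feeding-practices label, and drop or restate the claim that 0.0008 is the smallest level.
7. If a power gain from testing scores is cited, state the assumed effect sizes beside it.

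This changes wording only and needs no new data or participants. The cost is that no confirmatory claim can be made for a single item.

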## Background

Obesity prevalence among infants, toddlers, and preschool children in the United States (US) has doubled from the 1970s to the twenty-first century [1, 2]. Although rates have generally stabilized among some populations, racial/ethnic and socioeconomic disparities persist [3, 4]. For example, 9.4% of Latinx infants have a weight-for-length > 95th percentile relative to 6.6% of non-Latinx white infants. Although there has been a growing literature to better understand risk factors for obesity early in life, it remains unclear how feeding impacts early life risk for obesity among racial/ethnic minority children [5–9].

The American Academy of Pediatrics recommends exclusive breastfeeding as the optimal form of infant nutrition for the first 6 months and continued supplemental breastfeeding for 1 year. At 6 months, they recommend the introduction of a wide variety of nutrient-dense complementary foods. Starting at 9 months, they recommend three nutrient-dense meals and two or three small nutrient-dense snacks per day. Despite these guidelines racial/ethnic minority infants consume too many energy-dense foods and insufficient fruits and vegetables. Nationally representative research showed non-Latinx Black and Latinx infants between 6 and 11 months had lower intakes of fruits and vegetables and greater intakes of sweet and salty snacks compared to non-Latinx White infants [10, 11]. Research consistently shows common feeding practices deviate from these guidelines and are potential risk factors for early childhood obesity and targets for intervention: formula feeding, [12–16] combination feeding (breastmilk and formula), and the early introduction of solid foods [17, 18]. Other practices, such as early introduction of sugar sweetened beverages, are associated with obesity among older children and adults, [19] but their relation to obesity in infants is less explored [20, 21]. Research documents racial/ethnic disparities in these and related practices, such as feeding sugary drinks and “baby” cookies, [22] directing baby to empty the bottle, or propping the bottle [19, 23]. Such research offers insight into what infants are eating, but tells us little about how infants are fed.

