Generalized linear mixed models will be built to assess how the different constructs and/or sub-groups of feeding styles and practices relate to infant growth and obesity, adjusting for important covariates. We will employ Poisson regression to predict obesity, measured as the count of infants who became obese. The effect sizes for infant growth will be presented as how their weights change the score mean and/or summations of different constructs and their subgroups over time. The effect sizes for obesity will be presented as hazard ratios to evaluate comparative contributions of the construct and/or different sub-groups to obesity over time. Results of these analyses will be: 1) clustering of feeding style and practice items into subconstructs and subgroups which can be identified as meaningful clusters; 2) variation in feeding styles and practices within the sample; and 3) as whole latent variables, how these constructs or their subscales comparatively affect infant growth and obesity. This information will inform the development of the enhanced intervention components.

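### Obesity is defined by BMI at the 24-month visit but is to be reported as hazard ratios from a Poisson model; the outcome and effect measure should be matched, and the 292/80% figure should not be read as covering obesity

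*Protocol article*

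**What the plan says.** The Project overview (Phase 1 paragraph) sets the modelling aim as "infant growth from 2 to 24 months and obesity at 24 months". Survey measures names infant growth and obesity as the two dependent variables. It bases obesity at 24 months on BMI, which it calls "the standard clinical measure of obesity in children 2 years and older". The same section also says that WHO "weight-for-length z-scores at ages 2, 6, 12, and 24 months will be used to evaluate infant growth and obesity".

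The Statistical analysis section describes the obesity model in these words: "We will employ Poisson regression to predict obesity, measured as the count of infants who became obese". The effect measure follows: "The effect sizes for obesity will be presented as hazard ratios", with the stated purpose of comparing contributions to obesity over time.

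The sample-size paragraph of that section lists a two-sided alpha of 0.05, 80% power, a smallest Bonferroni-adjusted level of 0.0008 (0.05/63), a mixed-model R squared of at least 60%, and a hazard ratio of 1 for any reference level. From these it gives a sample size of 292. The planned cohort is 300 pairs.

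**The concern.** A hazard ratio compares rates of onset, so it needs a time to onset or at least an interval that contains it. BMI status at one visit supplies neither. The article describes no onset variable, no censoring rule and no survival model.

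A reader of the results would take a hazard ratio to mean that a feeding style brings obesity on faster. The planned model would show only that obesity at 24 months is more or less common.

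The reference hazard ratio of 1 in the sample-size paragraph also invites the belief that 80% power extends to obesity. This matters because obesity is one of two named dependent variables and part of the Phase 1 hypothesis. Items that are not strongly associated are to be dropped from further analysis, and the results are to inform the Phase 2 intervention.

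**Working it through.** **1. Outcome against effect measure.**
- If the outcome is 24-month BMI status, each child contributes one yes/no. A log-link Poisson model of it estimates the ratio of two risks. No hazard is involved.
- If the outcome is first classification as obese at 2, 6, 12 or 24 months, onset is known only to lie within gaps of 4, 6 or 12 months, and the state can reverse. A hazard ratio is then possible under assumptions, but only from a discrete-time or interval-censored model with onset defined. None is described, and this reading departs from the 24-month BMI definition.

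Neither reading supports the hazard-ratio label as the text stands.

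**2. How far apart the two measures can be.** Suppose that obesity is irreversible and hazards are proportional. The hazard ratio is then ln(1 − p1)/ln(1 − p0). With p0 = 0.0627 and p1 = 0.1253 (step 4) this is 0.1339/0.0647 = 2.07 for a risk ratio of 2. With p0 = 0.1133 and p1 = 0.2267 it is 0.2571/0.1203 = 2.14. The damage is mainly to interpretation, not to the size of the number.

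**3. The plan's figure of 292.** Taking R squared 0.60 as a multiple-regression effect size, f² = 0.60/0.40 = 1.5. For 80% power the noncentral-F calculation gives N = 8 (1 predictor) to 128 (111 predictors) at alpha 0.05, and 18 to 151 at 0.0008. None is 292. A hazard ratio of 1 is the null value and contributes no effect size. Values near 292 appear only with inputs that the article does not state; for example, f² = 0.0625 with one predictor at alpha 0.0008 gives 288. No obesity rate or alternative ratio is among the stated conditions.

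**4. Illustration of power for binary obesity.** None of these inputs is stated as a design input for obesity:
- Analysed: 300 × 0.86 = 258. The 86% is average retention in prior trials (Tracking and retention).
- Prevalence: 9.4% (Background: "9.4% of Latinx infants have a weight-for-length > 95th percentile"). The range runs from 6.6% (Background, non-Latinx white infants) to 17% (Sites and partnerships, ages 2 to 19 years).
- Half of mothers exposed, and a risk ratio of 2: my assumptions.

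Expected cases: 258 × 0.094 = 24.3. Lowest: 258 × 0.066 = 17.0. Highest: 300 × 0.17 = 51.0.

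Power by the Wald test on the log risk ratio, with n = 129 per group:
- p0 = 2 × 0.094/3 = 0.0627; p1 = 0.1253.
- SE = √[(1 − p0)/(n·p0) + (1 − p1)/(n·p1)] = √(0.1159 + 0.0541) = 0.412.
- ln 2/SE = 0.693/0.412 = 1.68.
- Alpha 0.05: Φ(1.68 − 1.96) = 39%. Alpha 0.0008: Φ(1.68 − 3.35) = 5%.

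| Analysed, prevalence | Cases | Power, alpha 0.05 | Power, alpha 0.0008 |
|---|---|---|---|
| 258, 9.4% | 24 | 39% | 5% |
| 258, 17% | 44 | 65% | 16% |
| 300, 17% | 51 | 72% | 21% |

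A two-proportion test gives 41% and 5% in the first row and 75% and 23% in the last, so the conclusion does not depend on the formula. By that test, with 258 analysed at 9.4%, 80% power needs a risk ratio of about 3.3 at alpha 0.05 and about 9.3 at 0.0008. These figures ignore site clustering, which would usually lower them.

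**The case against.** The strongest defence is that the article does not settle on a single-visit outcome. Survey measures evaluates obesity from z-scores at four visits, and the analysis section speaks of infants who became obese and of obesity over time. With four classifications, a discrete-time or piecewise-exponential model could yield hazard ratios under assumptions. This stands in part: a reader might infer that these data could never give a hazard ratio, and the documents do not support that. But no such model is described, and the four-visit reading conflicts with the 24-month definition.

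A reader might also infer that Poisson regression is the wrong model. It is not: with robust variance it is a valid route to risk ratios. The article does not state the variance type, which may be left to a fuller plan.

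On power, the 80% is tied to no named endpoint and no obesity effect size is given. The inference that about 24 cases disprove a claimed 80% for obesity therefore goes too far. The two-proportion test gives 88% for a risk ratio of 4 at alpha 0.05 with those same 24 cases. The case count applies a background infant weight-for-length rate to BMI status at 24 months in a mixed cohort. The equal-group contrast is not the planned test of five-level styles and composite practice scores. The level 0.0008 is the article's smallest, for single items. All of this stands, which is why the figures serve only as illustration.

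**Conclusion.** The concern holds in a limited form. The obesity outcome, its time point and its effect measure do not agree, and the model as described for 24-month status would give risk ratios labelled as hazard ratios. This rests on the text alone.

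The figure of 292 with 80% power cannot be shown to cover binary obesity, because no obesity rate or effect size lies behind it. Under the stated assumptions, power for a risk ratio of 2 is about 40% at alpha 0.05 and 5% at 0.0008. It stays below 80% at alpha 0.05 even in the most favourable case examined.

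This should be fixed but is not critical: Phase 1 is observational, the correction is mostly wording, and the Discussion has a fallback if Phase 1 findings cannot be used.

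**What to change.** - Name obesity at 24 months, yes or no per child, as the obesity outcome, and reconcile the four-visit sentence in Survey measures with it.
- Model it by log-link Poisson with robust variance, or by a log-binomial or logistic mixed model, keeping the planned allowance for site. Report risk ratios (or odds ratios for the logistic model).
- Replace the hazard-ratio wording in both places in the Statistical analysis section: the sample-size conditions and the obesity effect measure.
- If onset across the four visits is intended instead, define onset and use a discrete-time or interval-censored model.
- State that 292 and 80% rest on no obesity rate or obesity effect size and do not cover binary obesity.

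The cost is a change of analysis wording, with no new data or visits, and a more modest claim about obesity. The onset option would cost more, since it needs a definition and a model that the article does not yet contain.
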